### Recruitment {15}

#### School recruitment

Officials at local high schools in Nairobi and nearby areas will be approached by the researchers to participate in the study. The high schools will discuss study participation in a conversation guided by a flyer that will outline details about the study. From interested schools, we will select 5–12 high schools. The selection of the participating high schools will be done to ensure that there is a mix of boy schools and girl schools and a mix of national and county, and day and boarding schools. We will also take into consideration logistical considerations (i.e., if the group sessions in two selected schools can only occur at the same time, most likely only one of the two schools will be selected). Additionally, a small in-kind donation of materials worth no more than 200 USD will be provided to participating schools to thank them for the time and work they have invested in the study and contribute to student wellbeing.

#### Participant recruitment

Youth participants from up to 12 Kenyan high schools will be recruited by the Kenyan study team members (Co-PI [name] and [name]) from local high schools. The intervention will take place at these high schools during the school day. The exact time will be determined in consultation with the schools and will depend on the scheduling needs of each school. In all the participating schools, students attending high school will be notified about the study by the school headteachers and other administrators. The school administrators will then gather interested students in classrooms. Eligible students will be informed that participation is voluntary and that they can opt out at any time, as described in the Participant Flyer. They will also be provided with an opportunity to ask questions, after which they will also provide informed consent/assent. All interested students will then be asked to fill out a brief baseline questionnaire battery to assist with randomization. As compensation for participation, all study participants will receive notebooks and pens/pencils during the first intervention session and will receive an opportunity each week to raffle for small prizes such as t-shirts or water bottles each week.

## Assignment of interventions: allocation

### Sequence generation {16a}

After the baseline assessment, youths who opt to participate in the study will be randomly allocated within each school to one of the four intervention conditions or to the study skills control condition (with equal probability for assignment to each condition) using a computerized random number generator in R. Randomization will be stratified by reported age and gender in the case of mixed-gender schools, as well as by level of symptoms at baseline (i.e., GAD-7 and PHQ-8 scores).

### Concealment mechanism {16b}

All students at a given school who choose to enroll in the study will be randomized at the same time by an offsite researcher who is uninvolved in the study planning and implementation. There will therefore be no way for the study team to predict or influence which students will be assigned to which condition, to know the allocation sequence, or to know which students have been assigned to which conditions until the offsite researcher provides the team with a final, full list of student assignments.

### Implementation {16c}

An offsite researcher will generate the allocation sequence and assign participants to interventions using this allocation sequence. Then, researchers from the study team located in Kenya will randomly assign group leaders to lead certain groups, and will enroll students into these groups (in the appropriate condition assigned by the offsite researcher) at each school.

## Assignment of interventions: blinding

### Who will be blinded {17a}

Participants, lay providers, and study staff working with participants and lay providers cannot be blind to condition; however, lay providers and participants will not be informed of study hypotheses, and the study will be described as testing a series of interventions to understand their effects on wellbeing and academic performance. This should help conceal the control group.

### Procedure for unblinding if needed {17b}

Unblinding will only be necessary in the event of a safety concern; in these cases, only those involved in implementing the intervention on the ground (i.e., group leaders, clinical supervisors, and the expert clinician on the study team) will need to know the individual’s identity and group assignment. All others, including data analysts and those involved in entering data, will be kept blind, and we do not expect that unblinding will be necessary during the trial for these other members of the study team. Thus, we do not have unblinding procedures in mind for anyone except those involved in direct provision of emergency clinical services. Additionally, data collection procedures will ensure blindness in two ways: (a) no measure administrators will know what any student’s response was to any question, and (b) participants will be informed at the beginning of the assessments that their responses will be confidential in this way.

## Data collection and management

### Plans for assessment and collection of outcomes {18a}

As discussed under {12}, primary outcomes include participants’ severity of youth depression symptoms (as measured by the PHQ-8), levels of anxiety symptoms (GAD-7), academic performance (standardized scores representing students’ mean grades across enrolled subjects), and mental wellbeing (SWEMWBS). Secondary outcomes include participants’ character strengths related to wellbeing (per the EPOCH), perceived meaning and life purpose (PILS-12), gratitude (GQ-6), implicit theories of personality (IPTQ), use of intervention strategies, and personal satisfaction with social support (MSPSS). Measures of intervention acceptability and appropriateness among participants (AIM and IAM, respectively) will also be collected, along with basic demographic information (Demographic Questionnaire). The study team will also elicit program feedback from both study participants and group leaders. Study scales and questionnaires, as well as their reliability and validity, are further detailed under {12}.

Measures of demographic variables and primary outcomes will constitute one baseline data collection form, to be administered and collected by the study team immediately following the consenting/assenting process. Lay providers will then pass out baseline measures of secondary outcomes under supervision from study staff by asking participants to complete a separate questionnaire battery with primary outcomes immediately prior to the first intervention sessions. These same lay providers will administer, under the supervision of study staff, measures of primary outcomes and potential mediators (including some secondary outcomes) at the intervention midpoint, and all primary and secondary outcome measures and intervention feedback measures at the endpoint. Trained supervisors and the Kenyan study PI ([name]) and Co-I ([name]) will ensure data confidentiality and adherence to data collection protocols among lay providers at each of these stages. Supervisors will also collect physical questionnaires immediately from the group leaders, which trained study team members will scan and upload according to the procedures described under {27}.

Kenyan study team members (Co-PI [name] and Co-I [name]) will work with school officials to administer the 1-month, 3-month, 6-month, and 9-month follow-up data collection forms, which will include all primary and secondary outcome measures. We will access academic performance data for the three school terms before, during, and after the intervention through publicly accessible datasets provided to us by participating schools. Academic performance data will be standardized according to the process described under {12} and piloted in our initial RCT [20].

The study team will promote data quality by training lay providers and supervisors on adhering to intervention protocols and rules of trial conduct, including proper data collection techniques. Additionally, all those who interact with private participant data (e.g., those scanning and collecting questionnaires and working with unblinded datasets) will have up-to-date formal human subjects training certificates, either from their institution of affiliation or from the federal government. Enlisting independent raters to code randomly selected recordings of intervention sessions for lay provider performance and fidelity will further enhance data quality. See {11c} for more on the above. Finally, we will employ periodic data entry checks and will use range checks on all data, as described under {19}.

### Plans to promote participant retention and complete follow-up {18b}

Study team members will work with school officials to promote participant retention. School officials will help the study team remind participating students to attend intervention sessions at the scheduled times and attend follow-up data collection sessions. The study team will also conduct raffles of small prizes (e.g., water bottles and t-shirts) for participants during intervention sessions and provide a small gift to each school (in the form of an in-kind donation of materials including some to prevent the spread of COVID-19).

Participants who miss any intervention session(s), with the exception of the first which includes essential baseline data collection, will not be removed from the study nor barred from attending subsequent sessions. The study team will continue to collect measures completed by such participants during any sessions and follow-up points they attend; of course, participants can stop attending sessions at any time and for any reason. Because school grades are publicly accessible via participating schools, we will still collect school grades for any participant who discontinues or is removed from the intervention after the first session for any reason listed under {11b}, unless the participant explicitly withdraws consent to participate in the study, in which case their data will be removed from all analyses.

### Data management {19}

At each stage of the intervention and follow-ups, the study team in Kenya with the involvement of either school administrators or lay providers will administer paper questionnaires to study participants. Trained supervisors or other trained members of the study team (all of whom have completed research ethics courses online and with the study team in person) will collect questionnaires and immediately bring them back to a secure, locked room at the study headquarters. We will use a software called Papersurvey.io (which is fully compliant with the European Union’s General Data Protection Regulation) to automatically scan and upload physical questionnaires with a scanner stored in this same secure location. A study team member will periodically verify data automatically scanned into Papersurvey.io against physical questionnaire responses in order to ensure that no systematic data entry errors arise. In addition to random data checks, the study team will range check all data values in the full dataset. Full data storage, scanning, and uploading protocols to promote confidentiality for both paper and digital questionnaires are detailed under {27}.

### Confidentiality {27}

We will take several steps to maintain confidentiality, including keeping paper questionnaires in a private location, separating identifying information from sensitive participant data, and making only fully de-identified data public. Data in paper format will be stored in a private location in a locked room. Paper copies of study data will be associated with a participant ID number assigned by study staff. Exceptions to this rule include consent and assent forms, which will include participant signatures and will therefore be stored in a locked location separate from other study data.

As noted under {19}, we will use a software called Papersurvey.io (which is fully compliant with the European Union’s General Data Protection Regulation) to automatically scan and enter responses to paper questionnaires. Once these questionnaires have been entered using Papersurvey.io, the scanned questionnaires and databases will be deleted from the Papersurvey.io server and will be moved to a password-protected and encrypted study database.

All study data will be de-identified and stored in a password-protected and encrypted database only accessible to study staff. Study staff will have access to this database via confidential usernames and passwords. All questionnaires, copies of consent forms, and audio recordings of group sessions will be stored in this password-protected and encrypted database. Audio recordings that are not selected to be coded will be deleted, as will those selected to be coded at the conclusion of the study. Additionally, a list of participant names and corresponding ID numbers will be stored in a separate, password-protected folder of the study staff’s password-protected and encrypted electronic database. Any identifying features of participants will be removed from the aggregate data presented to those outside the study team (e.g., in posters or manuscripts). Lay providers will know participant names and the information participants choose to share with them but will not be informed about scores on other measures associated with these participants. They and other study staff will be trained in the importance of maintaining participant confidentiality.

### Plans for collection, laboratory evaluation, and storage of biological specimens for genetic or molecular analysis in this trial/future use {33}

N/A; this trial does not involve collection or analysis of biological specimens.

## Statistical methods

### Statistical methods for primary and secondary outcomes {20a}

Outcome measures will only be analyzed if they demonstrate internal consistency within the full sample at baseline, defined as an alpha value of .70 or above [75]. For those outcome measures that pass this threshold, all main analyses of primary and secondary outcomes will follow an intent-to-treat approach, meaning that all participants who consent, are randomized into the groups, and complete baseline measures will be included in all analyses (see 20c below for more about plans for handling missing data).

For all analyses of primary and secondary outcomes, we plan to use linear mixed effects models to model time × condition interaction with a random intercept for participant ID to allow for individual variation at baseline. We plan to control for age and sex in all models of primary and secondary outcomes. Age will be included because older adolescents report increased psychosocial stress and thus greater risk of mental illness [3]. Similarly, sex differences in anxiety and depression are widely documented in adolescents including Kenyan adolescents [3, 76]. Additionally, the authors will test more complicated random effects structures which reflect the hierarchical structure of the data, including random effects for groups within group leaders, crossed random effects for schools and group leaders, and for participants in groups. We will also test adding a random slope for participant ID and for school; however, these added random effects may result in overfitting, which would reduce the generalizability of our findings. If this is the case, we will select a more parsimonious model with a simpler random effects structure. These variables (group leader, school, and group) will also be tested as covariates rather than random effects in the model, and final model selection will be done taking into account both overfitting warnings and Akaike Information Criterion (AIC) [77].

Primary models will include all five groups, using the control group as the contrast group. Secondary models will include the four intervention conditions, using the full Shamiri intervention as the contrast group. Significant (*p* < .05 with a Holm-Bonferroni correction to account for four comparisons within each model) time × condition interactions will indicate that one condition produced significantly steeper improvements than another condition across the time included in the analyses. As described above and per recommendations outlined in past literature [78], the Holm-Bonferroni correction will be applied at a family-wise level (i.e., to account for multiple group comparisons on each outcome), rather than at a study-wise level.

Additionally, for all pairwise contrasts (including those comparing active interventions to each other) on all primary and secondary outcomes, effect sizes will be calculated as mean gain scores, to compare change within the various intervention and control groups.

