### Objectives {7}

The objectives of this study are threefold. First, we aim to compare the effects of each intervention and control condition on the primary outcomes (depressive symptoms, anxiety symptoms, academic performance, and wellness). We hypothesize that all the intervention groups will outperform the active control on each primary outcome. Second, we aim to compare the effects of each group on secondary outcomes (described below in {12}). Finally, in an exploratory fashion, we also aim to identify for whom these interventions are most effective and their mechanisms of change.

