##### Academic performance (average term grades)

Academic grades of the participants will be collected during (1) the school-term before the intervention (January to April 2021), (2) the school-term during the intervention (May to August 2021), and (3) the school-term after the intervention (September to November 2021). We will calculate the students’ average term grade (mean grade for each student across all enrolled subjects) to determine their academic performance per semester. Although the number of subjects per student differs across schools, students typically sign up for between 6 and 12 subjects. To compare students’ grades across different grade levels, academic subjects, and schools, we will use the standardization piloted in our pilot RCT to convert the academic grades to standard scores (M = 60, SD = 10, chosen arbitrarily and used in rescaling) [20]. We may also examine subject-specific scores in the same fashion, or Math and Science averaged scores separately from Humanities and Language averaged scores.

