##### Implicit Personality Theory Questionnaire-3

The Implicit Personality Theory Questionnaire (IPTQ) is a screening instrument used to assess the implicit theories of personality participants have about whether people’s attributes are fixed or malleable [26, 65, 66]**.** The IPTQ asks participants to indicate on a scale of 1 (really disagree) to 6 (really agree) the extent to which they acknowledge three statements: “You have a certain personality, and it is something that you can’t do much about,” “Your personality is something about you that you can’t change very much,” and “Either you have a good personality or you don’t, and there is really very little you can do about it.” The IPTQ score (ranging from 0 to 18) will be used to predict whether the person has a stronger entity (fixed) theory of personality or stronger incremental (malleable) theory of personality. The IPTQ has shown acceptable internal consistency across several studies, including studies assessing anxiety and depression symptoms in adolescents [23, 67].

##### Multidimensional Scale of Perceived Social Support – 8

The Multidimensional Scale of Perceived Social Support (MSPSS) measures personal satisfaction with social support [68]. It consists of three subscales: the “friends” subscale (which measures support from friends), the “family” subscale (which measures support from family), and the significant others subscale (which measures support from significant others). The MSPSS has previously demonstrated good internal reliability in previous studies of behavioral and psychosocial adjustment among Kenyan adolescents [3]. We will use the “friends" and “family" subscales of the MSPSS.

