##### Acceptability of Intervention Measure-4

The Acceptability of Intervention Measure (AIM) is used to determine the extent to which an intervention is perceived to be acceptable by its participants [69]. The AIM has four items rated on a 5-point scale; items are averaged for each scale to yield a total score, ranging from 1 to 5. The AIM has demonstrated strong psychometric properties, including validity, reliability, and responsiveness to change. This measure has been implemented in studies on Kenyan adolescents or those experiencing, or at risk of developing, mental health difficulties [70, 71].

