##### Mechanisms of Change

We will also include items designed to measure the extent to which participants have changed their thoughts and actions based on the character strength interventions. For each construct (gratitude, growth, values, and study skills), we will ask participants to complete two items designed to assess the extent to which participants have intentionally thought about the character strength or acted based on the character strength over the past 2 weeks (the items can be found in the supplemental materials). These items are intended to help us understand if the interventions produce their intended effect, as well as to understand potential mechanisms of change of each intervention.

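### The baseline-alpha rule in {20a} does not exempt the primary outcomes, so a primary scale just under .70 would lose its planned randomised comparison

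*Protocol article*

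**What the plan says.** Section {20a} opens with a condition: "Outcome measures will only be analyzed if they demonstrate internal consistency within the full sample at baseline". The same sentence then sets the threshold for that condition: "defined as an alpha value of .70 or above". It continues: "For those outcome measures that pass this threshold, all main analyses of primary and secondary outcomes will follow an intent-to-treat approach". It does not limit the condition to secondary outcomes or to multi-item questionnaires, and does not say what happens to a primary outcome that fails.

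Objectives {7} names the "primary outcomes (depressive symptoms, anxiety symptoms, academic performance, and wellness" and hypothesises a benefit of every intervention over control on each of them. Three are questionnaires: PHQ-8 (8 items), GAD-7 (7) and SWEMWBS (7). The fourth is school grades: "We will calculate the students’ average term grade (mean grade for each student across all enrolled subjects". These are then rescaled to a standard score.

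Two further statements carry no alpha condition. Outcomes {12} promises means and SDs for every outcome measure at every visit. The closing paragraph of {20a} promises effect sizes for every pairwise contrast on all primary and secondary outcomes.

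The section on secondary outcome measures includes some very short instruments. The IPTQ records "the extent to which they acknowledge three statements". For each construct under Mechanisms of Change, "we will ask participants to complete two items designed to assess the extent to which participants have intentionally thought about" or acted on the character strength. It also includes the AIM, which "is used to determine the extent to which an intervention is perceived to be acceptable by its participants", and its companion, the IAM.

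**The concern.** The rule makes analysis of an outcome all or nothing at a single cut-off, and the primary outcomes are inside it. A primary scale just under .70 would get no time-by-condition model, so the first objective would go unanswered for that outcome. A scale just over .70, with practically the same reliability, would be analysed in full.

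To the extent that low alpha reflects random measurement error, it costs a randomised comparison precision and shrinks the standardised effect, but does not create a difference between arms. Leaving the outcome out is therefore a larger loss than the problem it guards against.

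There is also a question of scope. Grades have no item scale for which an alpha is defined, and the AIM and IAM rate an intervention that students have not yet received at baseline. Alpha also depends on the number of items, so a uniform .70 is hardest to reach for the shortest measures. Among these are measures meant to show whether an element moved its own target.

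**Working it through.** **Nothing to reproduce.** The .70 is a chosen threshold, not a derived figure. The protocol gives no alpha for any scale, so the results below are ranges under assumption.

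**1. Statements side by side**

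| Section | What it commits to | Alpha condition? |
|---|---|---|
| Objectives {7} | Comparison of arms on each primary outcome | No |
| Outcomes {12} | Means and SDs for every outcome measure at every visit | No |
| {20a}, opening | Analysis only for measures with baseline alpha of at least .70 | Yes |
| {20a}, closing paragraph | Effect sizes for all pairwise contrasts on all primary and secondary outcomes | No |

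Once any measure falls below .70, these cannot all be carried out as written.

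**2. Chance that a primary scale fails**

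Inputs: n = 1288 (target) or 2147 (invited), both from Sample size {14}; k = 7 items (GAD-7, SWEMWBS); true alpha t assumed. By Feldt's result, (1 − t)/(1 − sample alpha) follows F with n − 1 and (n − 1)(k − 1) degrees of freedom. So

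P(sample alpha < .70) = P(F < (1 − t)/.30).

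For t = .71 the bound is .29/.30 = .967; for t = .72 it is .28/.30 = .933.

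| True alpha | n = 1288 | n = 2147 |
|---|---|---|
| .68 | 0.94 | 0.98 |
| .69 | 0.78 | 0.84 |
| .70 | 0.50 | 0.50 |
| .71 | 0.22 | 0.15 |
| .72 | 0.06 | 0.02 |
| .74 | < 0.001 | about 0 |

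With 8 items (PHQ-8) the results are nearly the same: 0.21 at .71 and 0.05 at .72 for n = 1288. A simulation of 1000 trials per value (n = 1288, k = 7) gave 0.79, 0.52, 0.21 and 0.04 at true alphas of .69, .70, .71 and .72, in agreement. A primary scale is thus at real risk only if its true alpha is about .72 or lower.

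**3. What changes at the cut-off**

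If unreliability is random error, the standardised effect scales with the square root of reliability. From .71 to .69 the ratio is √(.69/.71) = .986, an attenuation of about 1.4%. The rule moves from full analysis to none over that step.

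**4. How the threshold bears on short measures**

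For standardised alpha a with k items, the mean inter-item correlation needed is r = a/(k − a(k − 1)). With a = .70:

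| Measure | k | Calculation | r needed |
|---|---|---|---|
| PHQ-8 | 8 | .70/3.1 | .23 |
| GAD-7, SWEMWBS | 7 | .70/2.8 | .25 |
| PCSC, SCSC, GQ-6 | 6 | .70/2.5 | .28 |
| AIM, IAM | 4 | .70/1.9 | .37 |
| IPTQ | 3 | .70/1.6 | .44 |
| Mechanism pair | 2 | .70/1.3 | .54 |

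The AIM and IAM row only shows the effect of length, since a baseline alpha is not meaningful for them. The last row applies only if the two mechanism items are scored together, which the protocol does not say.

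**5. Measures that the rule does not fit**

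Grades do have a pre-intervention value, but it is one average over subject sets that differ between students (typically 6 to 12 subjects), and no alpha is planned for it. The AIM and IAM rate the programme received, and {18a} places intervention feedback measures at the endpoint. No sentence says outright that they have no baseline, and the schedule figure is not available here, so their timing is an inference.

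**The case against.** The strongest defence is that this is a sound screen, fixed in advance. It uses the pooled sample at baseline, and Participant timeline {13} places the primary baselines before allocation. It cannot favour an arm or respond to results. Low alpha in a new population can also mean that the items do not measure one construct, which is more than noise and a fair reason for caution. All of this stands.

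The evidence that a scale will fail is thin. PHQ and GAD-7 have been used with Kenyan adolescents. SWEMWBS is cited as widely used in the UK and in non-English-speaking countries as well as in South Africa. PILS-12 has not been used with Kenyan adolescents, but is said to have adequate internal consistency in adolescents elsewhere. The IPTQ is described as acceptable across several studies. The short PCSC and SCSC were built by factor analysis and graded response modelling. This stands too, and makes the risk conditional.

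A reader might go further in three ways that the documents do not support:

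- That a failing primary outcome would disappear from the report. Outcomes {12} would still give its means and SDs; what is lost is the model-based comparison.
- That grades, the AIM and the IAM are in practice barred from analysis. The rule was probably meant for multi-item questionnaires, and {18a} names the AIM and IAM apart from the secondary outcomes. This is a gap in the stated scope.
- That the rule biases the comparisons or invites selective reporting. A prespecified rule on pooled baseline data does neither.

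What the defence does not answer is why a primary outcome should go without its comparison, when the same caution could be given by reporting alpha beside the result.

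**Conclusion.** The point holds in a limited form. As written, {20a} lets a baseline alpha below .70 remove a primary questionnaire from the main models, with no fallback. That conflicts with Objectives {7}, with Outcomes {12} and with the effect-size commitment later in {20a}. The harm is a lost answer to a stated objective; the validity of the comparisons that are made is untouched.

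The size depends on alphas that the document does not give. Under the Feldt model the risk is about even at a true alpha of .70, small at .72 and negligible at .74 for the planned sample. The misfit with grades, the AIM and the IAM rests on a literal reading and, for the last two, on inferred timing. The heavier demand on the IPTQ is arithmetic; for the mechanism pairs it also assumes a combined score. Importance is moderate: a cheap improvement, not a defect that must be cured before the trial can be trusted.

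**What to change.** Amend {20a} as follows:

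- Analyse all four primary outcomes whatever their baseline alpha.
- Limit any alpha rule to multi-item secondary scales that have a baseline, and say that it does not apply to grades, the AIM or the IAM.
- Where the rule applies, use it to flag a result as measured with low reliability, not to omit it.
- Report alpha with its confidence interval for each scale.
- State that the descriptive results in Outcomes {12} and the effect sizes in {20a} cover all listed outcomes, so that the sections agree.

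The cost is a few lines of text, with no new data and no change to the sample size. The downside is that a noisier or less coherent scale may be reported; the accompanying alpha and caution deal with that.
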